### Consideration method for missing, unused or invalid data

Phase 2a:

No imputation will be realized in this study.

Patient who did not receive both doses (first cohort phase 2a and first 2 patients of the second cohort of phase 2a) or one dose (6 last patients of the second cohort of phase 2a and phase 2b), according to protocol or followed up until D8 will be replaced.

Phase 2b:

No randomized subject replacement is planned.

We do not expect missing data for the primary outcome.

All attempts will be made to collect all data per protocol. Any data point that appears to be erroneous or inexplicable based on clinical judgment will be investigated as a possible outlier. If data points are identified as outliers, sensitivity analyses may be performed to examine the impact of including or excluding the outliers. Any substantive differences in these analyses will be reported.

For the primary outcome, if patient is not followed up until D15 then, data will be imputed by a multiple imputation procedure and a sensitivity analysis will be performed on the imputation method,

For the analyses of the secondary outcomes that involve clinical score (i.e. the key secondary outcome and time to improvement), if a subject is discharged from the hospital without a previously or concurrently reported clinical score of 2 or 1, then their clinical score at the time of discharge will be imputed as 2, which is the highest value for a non hospitalized subject.

For the analyses of the secondary outcomes, the following imputation rules will be used for subjects who are lost to follow-up, terminate early from the study, or do not have further outcome data available after discharge for any reason:

• Days of Non-invasive ventilation/high-flow oxygen:

If the subject’s clinical status scale is 5 at the last observed assessment, then the subject will be considered to be on non-invasive ventilation/high-flow oxygen. The endpoint will be total days when assessments are available plus all imputed days following the last observed assessment.

If the subject is not on non-invasive ventilation/high-flow oxygen at the last observed assessment, then the subject will be considered to not be on non- invasive ventilation/high-flow oxygen for the remainder of follow-up. Thus, no additional imputed days will be added to the number of days recorded on available assessments.

• Days of intubation or mechanical ventilation:

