## Sample size calculation

In the phase 2b, about 398 randomized patients, 199 patients in each group, will be included.

Assuming a true treatment difference in clinical failure rate of 10% for XAV-19 added to SoC therapy compared to placebo added to SoC therapy where a rate of 20% is expected, a sample size of 398 participants provides at least 80% power that the primary analysis will be statistically significant at the two-sided 5% significance level.

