# General statistical considerations

## General Principes

### Confidence intervals and p-values

All applicable statistical tests will be 2-sided and will be performed using a 5% significance level.

No correction for multiple comparisons will be applied; all secondary objectives will be considered as exploratory and results were reported with only effect size estimates with their confidence intervals (CIs). All CIs presented will be 95%CI and 2-sided.

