### Primary and key secondary outcome

Subjects who withdrew their consent before Day 15 will be imputed using multiple imputation.

Subjects who are discharged but are subsequently re-admitted prior to Day 15 without a reported 8-point ordinal scale, their ordinal score will be imputed at 7, which is the highest value for a hospitalized subject.

For subjects who are discharged, if no visit is done at day 15 +/ 2 days then the reported ordinal score will be imputed at 2 (highest level for ambulatory patients).

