### Days of invasive ventilation/ECMO:

If the subject’s clinical status scale is 6 or 7 at the last observed assessment, then the subject will be considered to be on ventilation/ECMO through Day 29. The endpoint will be total days when assessments are available plus all imputed days following the last observed assessment.

If the subject is not on invasive ventilation/ECMO at the last observed assessment, then the subject will be considered to not be on ventilation/ECMO oxygen for the remainder of follow-up. Thus, no additional imputed days will be added to the number of days recorded on available assessments.

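### For the primary outcome, the SAP limits the protocol's multiple imputation to consent withdrawals, gives discharged patients fixed scores of 7 or 2, and does not carry over the planned sensitivity analysis

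*Combined protocol and SAP*

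**What the plan says.** **Protocol 7.2.4, on the primary endpoint of phase 2b:** "if patient is not followed up until D15 then, data will be imputed by a multiple imputation procedure and a sensitivity analysis will be performed". That sensitivity analysis concerns the method of imputation. The same section says that no missing primary data are expected. For secondary outcomes based on the clinical score, including the key secondary outcome, it sets a fixed score of 2 at discharge when no 1 or 2 has been reported.

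**SAP 5.4, Primary and key secondary outcome**, gives three rules:

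1. Consent withdrawn before Day 15: multiple imputation.
2. Discharged and then "re-admitted prior to Day 15 without a reported 8-point ordinal scale, their ordinal score will be imputed at 7".
3. Discharged: "if no visit is done at day 15 +/ 2 days then the reported ordinal score will be imputed at 2".

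**SAP 5.1, Respiratory failure or death:** scores of 5, 6, 7 or 8 count as failure, and one occurrence after baseline is enough. Under Days of Ventilation/ECMO, the SAP associates scores 6 and 7 with ventilator or ECMO days.

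**SAP 2.7:** "In the phase 2b, about 398 randomized patients, 199 patients in each group, will be included", with a 10-point difference "compared to placebo added to SoC therapy where a rate of 20% is expected". On that basis the section states that "a sample size of 398 participants provides at least 80% power". SAP 3.1: "All applicable statistical tests will be 2-sided and will be performed using a 5% significance level".

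**The concern.** The two documents treat the same patients differently on the confirmatory endpoint. Under the protocol, a discharged patient whose course to Day 15 is unknown is multiply imputed. Under the SAP, that patient is a certain failure if readmitted without a score, or is given a score that counts as no failure if the Day 15 visit is missed. The same database could therefore give two primary results.

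The score of 7 ignores the reason for readmission. The plan itself foresees non-respiratory causes: thrombotic events are a secondary endpoint, and serum sickness up to Day 28 is listed among the risks. A patient readmitted for either, with the scale left blank, would enter the primary analysis as a respiratory failure. Failures unrelated to respiratory status dilute the contrast between arms.

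The score of 2 errs the other way. The endpoint covers the whole interval to Day 15, and a filled-in Day 15 score carries no information on events between discharge and that day.

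**Working it through.** **Step 1: who gets what for the primary outcome.**

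| Patient | Protocol 7.2.4 | SAP 5.4 |
|---|---|---|
| Withdrew consent before Day 15 | Multiple imputation | Multiple imputation |
| Discharged, readmitted before Day 15, no score | Multiple imputation if not followed to Day 15 | 7 (failure) |
| Discharged, no Day 15 visit | Multiple imputation if not followed to Day 15 | 2 (no failure from that score) |
| Lost before Day 15, not discharged, consent not withdrawn | Multiple imputation | No rule |
| Sensitivity analysis on the imputation method | Yes | Not mentioned |

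The fourth row can occur: SAP 3.2 lists loss to follow-up before Day 15 as a major deviation, and SAP 4.2 tabulates withdrawals by investigator decision. The SAP rules also overlap. A discharged patient who then withdraws consent before Day 15 and has no Day 15 visit meets rules 1 and 3, with no order of precedence. The sensitivity analyses that the SAP does mention concern outliers (5.4) and center effects after convergence failure (5.2), not the imputation.

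**Step 2: consequence of a 7.** It lies in the range 5 to 8, and one such score after baseline is enough. Every case under rule 2 is therefore a primary failure.

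**Step 3: reproduce the planned size.** Inputs from SAP 2.7 and 3.1: 20% versus 10%, two-sided 5%, 80% power, 1:1. With pooled variance and no continuity correction:

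n = [1.960 × √(2 × 0.15 × 0.85) + 0.842 × √(0.20 × 0.80 + 0.10 × 0.90)]² / 0.10² = [0.990 + 0.421]² / 0.01 ≈ 199 per arm, 398 in total.

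Power at 199 per arm is 80.0%, so the plan's figure is confirmed and there is no reserve.

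**Step 4: illustrate rule 2.** Let r be the share of true non-failures recoded as failures, equal in both arms. The documents do not give r, so the values below are assumptions. The observed rate is p′ = p + r(1 − p).

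| Assumed r | Placebo | XAV-19 | Difference (points) | Extra failures, placebo / XAV-19 | Power at 199 per arm | Total N for 80% |
|---|---|---|---|---|---|---|
| 0 | 20.0% | 10.0% | 10.0 | 0 / 0 | 80.0% | 398 |
| 1% | 20.8% | 10.9% | 9.9 | 1.6 / 1.8 | 77.4% | 426 |
| 2% | 21.6% | 11.8% | 9.8 | 3.2 / 3.6 | about 75% | 454 |

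For example, at r = 2%: placebo 0.20 + 0.02 × 0.80 = 0.216; XAV-19 0.10 + 0.02 × 0.90 = 0.118.

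**Step 5: illustrate rule 3.** If the score of 2 hid an assumed 5% of true failures in each arm, the rates would be 0.20 × 0.95 = 19.0% and 0.10 × 0.95 = 9.5%, and power would be 77.6%.

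**The case against.** The strongest reply is that rule 2 will rarely apply. It needs discharge, readmission before Day 15 and a blank score together. The scale is scheduled daily to Day 29, Day 8 and Day 15 are on-site visits even after discharge, and hospitalisation is an SAE criterion with real-time eCRF entry. Some unscored readmissions will also be genuine respiratory failures, which a 7 classifies correctly. With equal rates in both arms, the false failures pull toward the null and do not inflate type I error. All of this stands, and it limits the size of the problem. It does not reconcile the two documents.

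Other readings go too far:

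- *The SAP abandons multiple imputation.* It keeps it for consent withdrawal. Fixed values are not new either: the protocol sets 2 at discharge for the key secondary outcome and leaves further detail to the SAP.
- *An imputed 7 also credits ventilation to Day 29.* That rule reads "clinical status scale is 6 or 7 at the last observed assessment, then the subject will be considered to be on ventilation/ECMO through Day 29". An imputed score is not an observed assessment, so on its wording the rule is not triggered.
- *A score of 2 erases an earlier failure.* One recorded failure is enough, so only unobserved time after discharge is affected.
- *The sensitivity analysis is cancelled.* The SAP is silent on it. The primary endpoint is also analysed on the mITT and PP sets, and PP leaves out patients lost or withdrawn before Day 15, but that does not test the imputation.
- *The Day 15 windows contradict each other.* One day either way governs visit conduct; two days governs data handling. A wider analysis window is not an inconsistency.

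**Conclusion.** The point holds in limited form. For the primary outcome, SAP 5.4 narrows the protocol's multiple imputation to consent withdrawals, turns an unscored readmission before Day 15 into a failure regardless of cause, and assumes no failure after discharge when the Day 15 visit is missing. It omits the protocol's sensitivity analysis on the imputation method and leaves one group of losses without a rule. These follow from the two texts and need no outside figure.

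The size is unknown and may be small. A fall in power from 80% to about 77% to 75% rests on an assumed 1% to 2% of true non-failures recoded, equally in both arms. A reader could obtain a larger loss by assuming a higher share, but nothing in the documents supports one. The case for change rests on having a single, defensible rule for a confirmatory endpoint before unblinding, not on a demonstrated loss of power.

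**What to change.** 1. For the primary and key secondary endpoints, replace the fixed 7. Classify each unscored readmission from the readmission or SAE record and the Day 29 contact, using the highest respiratory support up to the endpoint day. The Day 60 call should not be relied on, because SAP 2.6 plans unblinding once Day 29 data are complete.
2. For the primary outcome, apply multiple imputation as in protocol 7.2.4 to everyone whose status to Day 15 is still unknown. This includes discharged patients without a Day 15 contact and other losses to follow-up. State which rule takes precedence when more than one applies.
3. Restore the protocol's sensitivity analysis on the imputation method. The fixed values of 7 and 2 can serve as one scenario.

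The cost is SAP wording, some programming and a blinded look at the affected records, which could be added to the blind review of deviations already planned before database freeze. No new visits or data collection are needed, and the SAP already provides for multiple imputation.

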### Clinical severity – 8-point ordinal scale

Subjects who are discharged but are subsequently re-admitted without a reported 8-point ordinal scale, their ordinal score will be imputed at 7, which is the highest value for a hospitalized subject.

For subjects who are discharged, if no visit is done then the reported ordinal score will be imputed at 2 (highest level for ambulatory patients).

For subjects who are discharged from the hospital without a previously or concurrently reported clinical score of 1 or 2, then their clinical score at the time of discharge will be imputed as 2, which is the highest value for a non-hospitalized subject.

For time to event outcomes, subjects who are lost to follow-up or terminate the study prior to Day 29 and prior to observing/experiencing, the event will be censored at the time of their last observed assessment.

### Days of Non-invasive ventilation/high-flow oxygen:

If the subject’s 8 point ordinal scale is 5 at the last observed assessment, then the subject will be considered to be on non-invasive ventilation/high-flow oxygen through Day 29. The endpoint will be total days when assessments are available plus all imputed days following the last observed assessment.

If the subject is not on non-invasive ventilation/high-flow oxygen at the last observed assessment, then the subject will be considered to not be on non- invasive ventilation/high-flow oxygen for the remainder of follow-up. Thus, no additional imputed days will be added to the number of days recorded on available assessments.

### Days of invasive ventilation/ECMO:

If the subject’s clinical status scale is 6 or 7 at the last observed assessment, then the subject will be considered to be on ventilation/ECMO through Day 29. The endpoint will be total days when assessments are available plus all imputed days following the last observed assessment.

If the subject is not on invasive ventilation/ECMO at the last observed assessment, then the subject will be considered to not be on ventilation/ECMO oxygen for the remainder of follow-up. Thus, no additional imputed days will be added to the number of days recorded on available assessments.

### Days of Oxygen

If the subject’s 8 point ordinal scale is 4, 5, 6, or 7 at the last observed assessment, then the subject will be considered to be on oxygen through Day 29. The endpoint will be total days when assessments are available plus all imputed days following the last observed assessment.

If the subject is not on oxygen at the last observed assessment, then the subject will be considered to not be on oxygen for the remainder of follow-up. Thus, no additional imputed days will be added to the number of days recorded on available assessments.

### Days of Hospitalization

If the subject is discharged and no further hospitalization data are available, then the subject will be assumed to not have been readmitted. Thus, no additional imputed days will be added to the number of days recorded on available assessments. If a subject die while hospitalized, the number of days of hospitalization will be imputed as 28 days.

